## Abstract

**Background:**

Alcohol dependence is a common disorder with a continuum regarding severity. Most alcohol-dependent persons have a moderate level of dependence and live under socially orderly conditions. Treatment-seeking in this group is low, mainly due to stigma and because treatment options are seen as unappealing.

Alcohol is a relevant topic to discuss in many primary care (PC) consultations and PC is less stigmatizing to visit compared to addiction care units for people with alcohol problems. However, general practitioners (GPs) hesitate to engage in treating alcohol problems due to time constraints and lack of knowledge. Screening and brief interventions are effective for high consumers but there are few studies on dependence.

**Methods:**

This is a two-group, parallel, randomized controlled trial (RCT). The aim is to study whether an Internet-based Cognitive Behavioral Treatment (iCBT) when added to treatment as usual (TAU) is more effective than TAU only for alcohol dependence in PC. Two hundred and sixty adults with alcohol dependence will be included. Participants are randomized to iCBT and TAU or TAU only. The primary study outcome is alcohol consumption in grams per week and heavy-drinking days. Secondary outcomes include alcohol-related problem severity, number of diagnostic criteria for alcohol dependence, depression and anxiety symptoms, health-related quality of life and biochemical markers for high consumption and liver pathology. Data will be analyzed using mixed-effect models.

**Discussion:**

Internet-based interventions are attractive to, and have been shown to reach, people with alcohol problems. Yet there are no studies investigating the efficacy of Internet treatment of alcohol dependence in PC. In this study we hypothesize that iCBT when added to TAU will improve treatment outcome for alcohol dependence in PC, compared to TAU only. If effective, iCBT can be distributed to the public to a low cost for a stakeholder and has the opportunity to reduce both short-term and long-term public health costs.

**Trial registration:**

ISRCTN69957414. Retrospectively registered on 7 June 2018.

## Background

Alcohol dependence is a common disorder, leading to much suffering for the individuals as well as their families and the community. In a recent systematic analysis for the Global Burden of Disease Study 2016, alcohol is found to be a leading risk factor for global disease burden and causes substantial health loss [1]. It was found that the risk of all-cause mortality, and of cancers specifically, rises with increasing levels of consumption. The level of consumption that minimizes health loss is zero. Based on the net burden, 1 in 7 deaths in men and 1 in 13 deaths in women in the EU are estimated to be caused by alcohol consumption [2]. Alcohol-use disorders (AUD) have the second highest burden of disease of all mental disorders after depression, the highest in men [3].

A major problem is that most individuals with alcohol dependence are not reached with treatment. Alcohol dependence has the widest treatment gap between the number of individuals affected and the number in treatment [4]. Only around 10–20% seek help and treatment-seekers tend to have more severe dependence with co-morbid disorders and unstable social situation [5, 6]. Early interventions and formal treatment for AUD should be implemented to reduce high levels of adverse outcomes.

In previous studies from our group it was observed that most alcohol-dependent persons have a moderate level of dependence and live under socially orderly conditions [7]. Nevertheless, the main part of morbidity and mortality as well as community costs related to alcohol consumption occur in this large group with moderate dependence. The majority of affected individuals are reluctant to seek treatment in existing addiction care units, largely due to the stigma related to alcohol problems and treatment [8]. An aim for this project is to study outcomes from treatment in a context that is perceived as less stigmatizing.

One possible way of reducing stigma is treatment in primary care (PC). Studies indicate that people with AUD are positive to seeking treatment in primary care [8]. Heavy alcohol use causes or complicates many diseases and conditions and is consequently relevant to discuss in many PC consultations [9]. In addition, a large proportion of individuals with alcohol dependence are already present in PC for the treatment of other conditions [4]. Previous positive studies in PC have mostly involved hazardous drinkers and it is unclear whether dependent individuals have been included in the studies [10]. General practitioners (GPs) are at present reluctant to engage in this area, mostly due to time constraints and uncertainty regarding their competence in this field [11]. However, in a previous study on treating alcohol dependence within PC, the GPs reported that it was less complicated than anticipated to treat alcohol dependence [12]. In this study a program for brief intervention and pharmaceutical treatment tailored to the primary care setting for treating alcohol dependence was developed. Participants were randomized to treatment in PC or an addiction clinic. In this study treatment in specialized care was not superior to PC [13].

Internet-based interventions have been shown to be attractive for, and to reach, persons with alcohol problems [14]. Internet-based treatments also have the advantage of high availability with the potential of attracting participants who would otherwise not participate in treatment due to practical concerns or time constrains [15]. Interventions can be delivered to many persons simultaneously regardless of the time of the day and geographical location, may be cost-effective and reduces stigma [16]. Most Internet studies so far have involved hazardous drinkers in student or general populations [17]. Internet-based approaches have shown similar efficacy as face-to-face treatment [18]. Web-based advice to reduce drinking among hazardous drinkers has been successfully implemented in PC in a project in Italy [19].

To date, there are no randomized controlled trials of Internet-based approaches for alcohol-dependent patients in PC.

### Aims and research hypothesis

The overall aim of this project is to study new approaches to improve the identification and treatment of alcohol dependence in PC. Specifically, the aim is to investigate the efficacy of an Internet-based CBT program for alcohol-dependent patients in PC.

The research hypothesis for the project is that:

Internet-based Cognitive Behavioral Treatment (iCBT), when added to treatment as usual (TAU) for alcohol dependence in PC, will reduce alcohol consumption more than TAU only.

## Methods

We adhered to the Standard Protocol Items Recommendations for Interventional Trials (SPIRIT) guidelines in the preparation of this protocol (see Fig. 1 and Additional file 1 for the SPIRIT Figure and Checklist, respectively).

**Fig. 1 Fig1:**
[figure not shown]
Standard Protocol Items: Recommendations for Interventional Trials (SPIRIT) Figure

### Setting and participants

Project coordination will take place at “[name]: Clinic for Alcohol and Health”, an outpatient alcohol clinic located in Stockholm specializing in treating AUDs and part of the Stockholm Center for Dependency Disorders. We collaborate with a number of PC clinics within Stockholm County in the study. Participants are informed about the study through the leaflet “Feel better with less alcohol”, distributed at the registration desk of the PC study sites to all patients > 18 years of age over a time period. Patients are also recruited via advertisements placed in waiting rooms at the participating PC clinics and via advertisements on the Internet and in local newspapers. Participants must be listed on and have their GP in one of the collaborating PC clinics.

#### Inclusion criteria

Participants have to meet criteria for alcohol dependence, based on the *International Statistical Classification of Diseases and Related Health Problems – Tenth Revision* (*ICD-10*). Participants also have to meet the threshold for hazardous drinking, which is defined as six or more points for women and eight or more points for men on the Alcohol Use Disorders Identification Test (AUDIT) [20].

#### Exclusion criteria

Individuals with serious mental illness, including substance-use disorder other than alcohol or nicotine, persons deemed in need of specialist treatment in psychiatry or dependence care, cognitive impairment and lack of knowledge of the Swedish language will be excluded.

#### The web-based treatment platform

We have built a web-based treatment platform with questionnaires for initial assessment and follow-up and a series of treatment modules based on cognitive behavioral therapy (CBT) and motivational enhancement therapy, here called Internet-based Cognitive Behavioral Treatment (iCBT). Prior to starting the randomized controlled trial (RCT), a pilot study (*n* = 3) was conducted involving an intervention identical to that used in the present study. The purpose was to test the study protocol, the Internet assessment procedure and the web-based treatment platform to obtain feedback from the patients on the feasibility.

### Study design

This is a multi-center, two-group, parallel, RCT to compare the effects of two 12-week interventions: Internet-based Cognitive Behavioral Treatment (iCBT) plus treatment as usual (TAU) or TAU only, designed to demonstrate statistical superiority. The proposed flow of participants through the trial is shown in Fig. 2. Assessments and biomarkers are completed by all participants at baseline (pre randomization) and post treatment at week 13 and week 52.

**Fig. 2 Fig2:**
[figure not shown]
Participant flow diagram

### Procedure

#### Recruitment

The personnel at the PC clinics are asked to encourage all patients attending the PC clinic under the time period to log on to the website indicated on the leaflet. Individuals interested in participating click on a link to the study registration site. Here the participants are provided with information about the study, they sign an informed consent, leave their data on demographics and contact information. Participants provide an e-mail address for communication.

#### Screening and baseline assessment

Initially a web-based screening assessment takes place. Individuals whot fulfill the inclusion criteria (alcohol dependence and hazardous consumption) are automatically invited to complete baseline assessment. Individuals that do not fulfill the inclusion criteria are excluded and guided to where to get further help.

After completion of self-assessment on the website an extended telephone screening with a research nurse takes place to assure data quality and completeness. In the telephone conversation the research nurse goes through the exclusion criteria. Individuals that meet the exclusion criteria are advised to seek appropriate action.

#### Randomization, treatment allocation and blinding

The randomization was done in blocks of 20 according to a fully automated and concealed procedure in the online platform that was programmed in the content management system Drupal (drupal.org) by the fourth author. The research nurse randomizes all eligible participants via the online platform by activating a link that only she has access to. Type of treatment (iCBT + TAU vs TAU) is not blinded neither for the participants nor the research nurse. Hence, unblinding of participants and the research nurse will not be necessary during the trial. Responsible researchers as well as data analysts will not have access to the codes concerning which experimental condition the participants participate in until after completion of analysis of the primary outcome measure. Hence, the risk of bias in the interpretation of the study’s result is minimal.

The participants are informed by the research nurse about their group allocation and are scheduled for a blood test for biomarkers and an appointment with the GP at the PC clinic, ideally within 2–3 weeks. The GPs give all participants feedback on the assessment and biomarkers and design a treatment plan based on current routines at the PC clinic. For those randomized to iCBT, the Internet program will be made available the following Monday after randomization.

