### Statistical analyses and sample size calculations

Baseline participant characteristics stratified by treatment group will be presented. Group differences will be tested using a *t* test for continuous variables and chi-square tests for categorical outcomes. Multiple imputation will be used to replace missing internal values where appropriate. Within-group changes in the primary outcome (alcohol consumption) and secondary outcomes (*ICD-10* criteria, AUDIT scores, depression, anxiety, EQ-5D-5 L and biomarkers) at 12 and 52 weeks will be analyzed according to the intention-to-treat principle, using linear mixed models and Poisson regression where appropriate. The models will further be adjusted for baseline covariates and treatment adherence. Per-protocol analyses will also be presented. All tests will be two-sided and *p* values of less than 0.05 considered statistically significant.

The study is designed to demonstrate statistical superiority. An effect-size of 0.61 has been shown in previous Internet studies on high consumers in the general population [25]. Due to a lack of studies on alcohol-dependent patients, our estimate is based on a more conservative effect-size of 0.4, which requires the estimated sample size of 100 participants in each arm to get a power of 80% and a statistically significance 0.05 when using a *t* test. Given an estimated dropout in iCBT of 30%, 260 participants are included in the study [26].

No interim analyses are planned.

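### With a fixed block of 20, the unblinded nurse who screens for exclusions and activates the randomisation link could predict late-block allocations if she knows the block size

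*Protocol article*

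**What the plan says.** Under Randomization, treatment allocation and blinding, the article gives one block size and calls the procedure automated and concealed: "The randomization was done in blocks of 20 according to a fully automated and concealed procedure in the online platform". It does not mention varying the size.

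The same section describes the nurse's part. She alone controls when an allocation is drawn: "The research nurse randomizes all eligible participants via the online platform by activating a link that only she has access to". Neither she nor the participants are masked to the arm; on this the article says: "Type of treatment (iCBT + TAU vs TAU) is not blinded neither for the participants nor the research nurse". She also passes on the result: "The participants are informed by the research nurse about their group allocation".

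Under Screening and baseline assessment, people who meet the inclusion criteria "are automatically invited to complete baseline assessment", so that step leaves no discretion. The exclusions are handled differently: "In the telephone conversation the research nurse goes through the exclusion criteria". Under Exclusion criteria, the list includes "persons deemed in need of specialist treatment in psychiatry or dependence care", alongside serious mental illness and cognitive impairment. Such items call for judgement.

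The masking that the article describes covers the responsible researchers and the data analysts. It does not cover the nurse.

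**The concern.** Concealment has two parts. The next allocation must not be readable from a list, and it must not be deducible from allocations already made. An automated platform secures the first. A fixed block length leaves the second open to anyone who sees every past allocation and knows the length. Here the role that sees every allocation is also the role that applies the exclusions and decides when the link is activated.

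A person near the boundary of needing specialist care is plausibly a heavier drinker with a worse outlook. If such people were excluded or deferred more often when one arm was expected next, the arms would differ in prognosis at entry. The primary outcome is self-reported drinking in a trial that is open to participants, so an imbalance of that kind could pass for a treatment effect or hide one.

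**Working it through.** The article gives no figure for predictability, so there is none to reproduce.

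**Inputs**
- Block length 20 (Randomization, treatment allocation and blinding).
- Total 260 participants (Statistical analyses and sample size calculations), so 260 / 20 = 13 complete blocks.
- Ratio 1:1, inferred from the equal arms in the sample size statement ("requires the estimated sample size of 100 participants in each arm to get a power of 80"). Each block is then 10:10.
- Assumed, not stated: the nurse knows the block length, keeps the running count, and works with a single sequence.

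Write the block as 2m with m = 10.

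**Step 1: allocations that are certain.** Once one arm has used its m places, the rest of the block is known. The expected length of that tail is 2m/(m+1) = 20/11 = 1.82 per block. As a share this is 1.82/20 = 9.1%, and over 13 blocks it is 23.6, about 24 of 260. The last place of every block is always known, so at least 13 allocations are exposed.

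**Step 2: correct guesses overall.** Always guess the arm with more places left. Expected correct guesses per block are

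m + 2^(2m−1)/C(2m,m) − 1/2 = 10 + 524,288/184,756 − 0.5 = 10 + 2.84 − 0.5 = 12.34.

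That is 12.34/20 = 61.7%, against 50% by chance. An exact recursion over the places remaining gives the same 12.34 and 1.82.

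**Step 3: where in the block this falls.**

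| Position | Correct guess |
|---|---|
| 1–15 (average) | about 57% |
| 16–17 | 66.7% |
| 18–19 | 73.7% |
| 20 | 100% |

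Check at position 19, with two places left: the chance that they are one of each arm is 2 × C(18,9)/C(20,10) = 2 × 48,620/184,756 = 0.526. The guess is therefore right with probability 0.474 × 1 + 0.526 × 0.5 = 0.737. The last five positions contribute 2 × 0.667 + 2 × 0.737 + 1 = 3.81 correct guesses, which leaves (12.34 − 3.81)/15 = 57% for the first fifteen.

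**Step 4: comparison.** A fixed block of 4 would give 70.8% correct and 33% certain. A block of 20 is much better, but it is not proof against counting.

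**Step 5: effect of varying the block size.** Simulated sequences of 260, with a guesser who knows the possible sizes but not the size of each block:

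| Sizes | Certain | Correct guess |
|---|---|---|
| 20 only | 9.1% | 61.7% |
| 16, 18, 20, 22, 24 | about 0.2% | about 61.5% |
| 10, 20, 30 | 1.6% | 61.3% |
| 4, 6, 8 | 2.2% | 68.0% |

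Varying the size removes nearly all certainty but hardly changes probabilistic guessing. Small varied blocks would make guessing easier than it is now.

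**The case against.** The strongest reply is that the route depends on knowledge the article does not attribute to the nurse. It does not say that she knows the block length, and it does not exclude it. Publication tells her little: the first protocol version is dated 5 June 2019, about 21 months into recruitment that ran from September 2017 to December 2019. A single sequence is also an inference, because a condensed article may leave stratification to the full protocol. So is the idea that the nurse alone decides the exclusions: the article says that she goes through them, and does not say who does the deeming. All of this stands, and the point is conditional for that reason.

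A second reply is that 20 is already a large block. That also stands: for the first three quarters of each block even a perfect record-keeper does little better than chance.

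Two stronger readings are tempting, and the document supports neither.
- A reader might infer that the article declares the risk of selection bias to be minimal. That remark follows the sentence on researchers and analysts lacking the codes, and it concerns interpretation of the results. It makes no claim about entry to the trial.
- A reader might infer that nothing later in the trial could correct a selective entry. But assessments are completed before randomisation, the primary outcome is change from baseline, and the models are to be adjusted for baseline covariates. Phosphatidylethanol and the liver enzymes are objective secondary measures. Baseline drinking, AUDIT score and ICD-10 criteria would capture much of the measured severity. What adjustment cannot reach is an unrecorded impression formed on the telephone.

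**Conclusion.** The point holds in conditional form and is modest in size. The protocol fixes one block length and places telephone screening, activation of the link and knowledge of all past allocations with one unblinded role. If the nurse knows or infers the block length, and there is a single 1:1 sequence, about 24 of 260 allocations are certain in advance and 61.7% can be guessed, mostly through the last five places of each block. Calling the procedure concealed does not answer this, because the prediction comes from counting and not from seeing the list.

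A reader might go further and conclude that selection took place. The document cannot show that, and no effect on the treatment estimate can be calculated from it. The finding is an avoidable weakness that is cheap to reduce while recruitment is still open.

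**What to change.** For participants not yet randomised:
1. Have the platform draw block sizes at random from a set of fairly large values. The sizes should not be disclosed to the nurse or published before recruitment ends.
2. Have the platform require a time-stamped, locked yes/no entry for each exclusion criterion before the link activates, and randomise immediately afterwards. This limits deferral and makes exclusions auditable. It does not stop a judgement coloured by expectation before the entry is made.
3. Add a sentence to the protocol saying how the nurse is kept from anticipating allocations.

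For participants already randomised, tabulate telephone-stage exclusions by date, matched to the block position open at that time. Excluded people have no block position of their own, so this is possible only if the dates were logged.

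**Cost:** a small change to a platform that already automates inclusion screening and randomisation, with no extra staff or participants. The final arm sizes may be slightly more unequal. The protection reaches only the remaining months of recruitment, and it removes certain predictions rather than educated guesses.

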#### Program engagement

Program engagement will be measured by automatic data collection on number of assignments accessed, tasks completed. Association between program engagement metrics and treatment outcomes will be explored.

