## Data Availability

During the trial, all patient data will be kept in a secure room accessible only by the research group, following standard protocols recommended by the Karolinska Institutet. Participant-level data and statistical codes are available on reasonable request according to the regulations of the responsible organization. All data are stored in a secure database available only to the research team. An external data monitoring committee or auditing were not deemed necessary due to the minimal risks involved, because data registration is done automatically in the online platform where all data are stored. The online platform is maintained and updated weekly. Data from blood samples are collected directly from the patient data file system at the PC clinics. All the data management procedures were monitored by the author group.

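### Analyst blinding until the primary analysis is complete is not secured, because the primary-outcome models are adjusted for adherence and the only adherence-type data described come from the iCBT arm

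*Protocol article*

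**What the plan says.** Under *Randomization, treatment allocation and blinding*, the protocol article says that type of treatment "is not blinded neither for the participants nor the research nurse". For those who analyse and interpret the data it sets a different rule: "Responsible researchers as well as data analysts will not have access to the codes concerning which experimental condition the participants participate in". The restriction lifts once the primary outcome has been analysed. From this it concludes that bias in interpreting the result is minimal.

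Under *Statistical analyses and sample size calculations*, alcohol consumption is named as the primary outcome. It is listed with the secondary outcomes as a subject of intention-to-treat linear mixed or Poisson models. The text continues: "The models will further be adjusted for baseline covariates and treatment adherence". It then adds: "Per-protocol analyses will also be presented". Neither sentence makes an exception for the primary outcome or places these analyses before or after the codes are released.

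Under *Program engagement*: "Program engagement will be measured by automatic data collection on number of assignments accessed, tasks completed". The section on the Internet program gives it to the intervention group only. TAU goes to both arms.

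**The concern.** The masking rule and the model specification sit in different sections and appear not to have been checked against each other. Withholding the codes masks an analyst only if nothing else in the analysis file identifies the groups. A covariate that can take non-trivial values in one arm alone does identify them.

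What is at stake is the credibility of the masking claim. The statistical section leaves several choices to judgement: when to impute, when to use a linear and when a Poisson model, and which baseline covariates to include. Masking is meant to stop such choices, and the reading of the result, from being steered towards a known arm. If the groups are identifiable while the choices are made, a report could describe a blinded primary analysis that was not blinded in practice.

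**Working it through.** The point turns on no figure, so the check sets the statements side by side.

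**Inputs**

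| Item | What the protocol article gives | Section |
|---|---|---|
| Who is masked | Researchers in charge and data analysts | Randomization, treatment allocation and blinding |
| End of masking | Completion of the primary outcome analysis | Same |
| Models affected | Mixed or Poisson models, primary outcome included | Statistical analyses and sample size calculations |
| Adjustment | Baseline covariates and adherence, no exception stated | Same |
| Definition of adherence | None | – |
| Adherence-type data described | Automatically logged use of the Internet program | Program engagement |
| Who can generate those data | Participants given iCBT | Internet-based Cognitive Behavioral Therapy |

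**Step 1. Does the adherence adjustment reach the primary outcome?** Yes, as written. The adjustment sentence refers back to the models just described, and these include alcohol consumption.

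**Step 2. Which data would supply the covariate?** The article describes one source, logged program use. It describes no measure of adherence to TAU, such as attendance at the GP appointment. That adherence means program use is therefore an inference, but it is the only reading for which the article describes any data.

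**Step 3. What does the analyst see?** Suppose the file has a masked label (A or B) and a usage field.
- If usage is blank for people without the program, the blanks fill one group.
- If usage is stored as a count, one group is zero throughout and the other contains positive values. An iCBT participant who never started also scores zero, so a single zero does not reveal that person's arm. But one positive value in a group is enough to identify that group, and with it the direction of the treatment contrast.

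In both cases the label is decoded without the allocation codes.

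**Step 4. When does this happen relative to the end of masking?**
- *Reading 1:* the adherence-adjusted model is part of the primary analysis. The groups are then identified before that analysis is complete, and the masking rule is broken by the plan's own model.
- *Reading 2:* the unadjusted or baseline-adjusted comparison is the primary analysis, and adherence enters only afterwards. Masking can then hold to the stated point.

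The text does not choose between the two. The same question arises for the per-protocol analyses: if the per-protocol set is defined by program use, building it before the lock reveals the groups in the same way.

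**The case against.** The strongest reply is that the statistical section can be read as a sequence: intention-to-treat models first, further adjustment next, per-protocol results in addition. On that reading the base comparison is completed under masked labels, and usage data and codes are released afterwards. The existing text permits this. The reply stands against any claim that the blinding is impossible. It does not settle the matter, because the order is never stated and the adjustment is written as a property of the models themselves.

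A second reply is that adherence is undefined and might include contact under TAU, and that program engagement is described as something to explore, not as the adherence covariate. This is fair. It makes the conflict conditional, but it does not supply another source of adherence data.

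A third is that data flow and masked extracts are details an article leaves to the full protocol or analysis plan. That is right for an omission. Here, though, the article makes a positive masking claim, draws a conclusion about bias from it, and states a model that may undercut it.

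Some stronger readings are tempting and are not supported:
- *That the team's access to the database already unblinds the analysts.* The data availability statement limits access to the team. It does not say that analysts see codes or usage tables, and the specific rule on the codes still governs.
- *That the author who programmed the platform is unblinded.* The article describes an automated, concealed procedure that the research nurse activates. It does not say that the programmer sees allocations or takes part in the analysis.
- *That analyst masking is the sole protection.* Allocation is concealed and no interim look is planned.
- *That a false-positive rate can be attached to the problem.* Picking the most favourable of several analyses is possible with A/B labels too, so such a figure would measure analytic flexibility and not the loss of masking.

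**Conclusion.** The concern holds in conditional form. The stated masking of analysts and the adherence-adjusted models for the primary outcome conflict if that adjustment belongs to the primary analysis, and the article leaves this open. The conclusion rests on two assumptions: that treatment adherence means use of the Internet program, and that the adjusted model is fitted before the primary analysis is declared complete. If either fails, masking can survive.

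The size cannot be put as a number from the document. In scope it touches both primary measures (weekly grams and heavy-drinking days) at both follow-ups. In kind it concerns analysis decisions and interpretation only. Participants and the research nurse are openly unblinded, so analyst masking never protected the self-reported drinking data. It would go too far to conclude that the blinding cannot hold or that it was in fact broken. What can be said is that the plan does not secure a safeguard it claims, and that this is worth correcting because the correction is easy.

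**What to change.** Add matching statements to the blinding section and the statistical section:

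1. The primary between-arm analysis of alcohol consumption is run and locked on data labelled A and B, in a file with no adherence, engagement or other field that exists only for iCBT.
2. Adherence-adjusted models and per-protocol analyses form a second step, begun only after the primary result is locked.

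This changes the primary model as now written, since adherence leaves it, and gives the masking rule a clear end point that the analysis can respect. The cost is a few sentences and one filtered data export. The small downside is that the adherence-related and per-protocol results come later.
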